### Educational Intervention

The therapist will go to each participant's home and perform an ergonomic assessment of the home. The therapist will also assess the execution of ADL by the participant using the home therapeutic advice for people who suffer stroke (HTAS) tool, which is a checklist of 60 items—the therapist will mark those items he valued as deficient. Later, with the experimental group, the therapist will mark on the participant’s advice sheet those items that were rated negatively and will advise them on how to solve these shortcomings. With this advice, the therapist will educate participants on the correct or easiest way to perform their daily tasks, on which adaptations they should make at home, and on what kind of technical assistance could be useful for them. Previous studies on the impact of stroke in patients have demonstrated that cognitive, communication, and physical weakness combined with environmental changes frequently cause changes in roles, routines, and daily occupations [8-11].

In stage 2 of the study, the app will be installed on the mobile phones of participants in the mobile phone group, which will remind them of the advice previously offered by the therapist. The timing of reminders will differ for each participant depending on the amount of advice they received. However, in the 18 weeks of the app being used, each piece of advice will be given as a reminder three times. The mobile phone will beep once for each piece of advice and the participant must check and mark the option indicating whether he has complied with the advice or not. Participants who will take part in the app intervention will have to answer at least 80% of the messages.

The app used in the study is called isoTimer (see Figure 1) and will be installed on participants’ phones who have a mobile phone with Android OS 3.2 or higher. For correct use of the app, the Google Calendar app will also be installed through which educational advice will be implemented and synchronized on the day and time scheduled by the researcher.

Because of the complications that can occur in this population with the use of mobile phones, the app has been designed to open and start working automatically when the mobile phone is switched on. At no time does the participant have to open the app.

The app works as a reminder, so that the daily educational advice will appear on the screen and the participant must indicate whether the task has been carried out. These responses will be saved in the participants’ mobile phones and then the researcher will download them to be added to the database.

### Ethical Considerations

To carry out this study we will follow the guideline for Good Clinical Practice (GCP) from the International Conference on Harmonisation (ICH), thus guaranteeing protection of the rights, safety, and welfare of trial subjects in accordance with the principles of the Declaration of Helsinki. This will also guarantee the credibility of the clinical trial data.

Before any intervention, each participant and his/her family will be presented with an information sheet and an informed-consent form. This form will explain the study (the voluntary nature thereof), the protection of personal data in accordance with the Organic Law on Personal Data Protection 19/55, as well as their freedom to leave the study at any time they choose.

When the agreement is signed, a copy will be given to each participant, which they will hand in at the clinical trial.

**Figure 1 figure1:**
[figure not shown]
Screenshot of the app isoTimer.

### Outcome Measure

The outcome measure of this study will allow us to know and assess the level of patient dependency, cognitive ability, quality of life, social support, and physical condition. All of these factors will be measured by the Barthel Index, the Functional Independence Measure, the Mini-Mental State Examination, the Canadian Neurological Scale, the Stroke Impact Scale-16, the Trunk Control Test, the Modified Rankin Scale, the Multidimensional Scale of Perceived Social Support, the Quality of Life Scale for Stroke, the Functional Reach Test, the Romberg Test, the Time Up and Go test, the Timed-Stands Test, a portable dynamometer, and a sociodemographic questionnaire (see Table 1).

In addition, visits to the emergency department, the general practitioner, and specialists after discharge from hospital to home, as well as taking drugs associated with stroke, will be controlled.

**Table 1 table1:** Outcome measures of the study.

Test or scale (acronym), reference	Measure	Items, n	Statistical treatment, reference	Variable type
Barthel Index (BI) [39-41]	Level of dependence	10	κw=.93 (95% CI 0.90-0.96) random effects modeling [42,43]	Main
Functional Independence Measure (FIM) [39]	Level of dependence	18	ICC^a^=.124-.661 [44]	Secondary
Mini-Mental State Examination (MMSE) [38]	Cognitive disability	11	ICC=.69 [45]	Secondary
Canadian Neurological Scale (CNS) [46]	Cognitive and motor function	7	κ= 0.76 [47]	Secondary
Stroke Impact Scale-16 (SIS-16) [48]	Quality of life	16	ICC=.70-.92 [49]	Secondary
Trunk Control Test (TCT) [50]	Trunk control	4	ρ=.76, *P*<0.001 [51]	Secondary
Modified Rankin Scale (MRS) [52]	Functional independence	1	Rater 1: κ=.81, .94 and Rater 2: κ=.95, .99 [53]	Secondary
Perceived Social Support Scale (MSPSS) [54,55]	Social support	12	ρ=.72-.85 [54]	Secondary
Quality of Life Scale for Stroke (ECVI-38) [56]	Quality of life	38	ICC=.81-.96 [56]	Secondary
Functional Reach Test (FRT) [57]	Stability	NA^b^	ICC=.90-.95 [58]	Secondary
Romberg Test (RT) [59]	Balance	NA	ICC=.84-.97 [60,61]	Secondary
Time Up and Go (TUG) [62]	Balance, mobility, and fall risk	NA	ICC=.96 [58]	Secondary
Portable dynamometer [63]	Strength in the upper limbs	NA	ICC=.98 [60]	Secondary
Timed-Stands Test (TST) [64]	Strength in the lower limbs	NA	ICC=.994 [65]	Secondary
Sociodemographic questionnaire	Sociodemographic data	25	NA	Secondary

^a^interclass correlation (ICC).

^b^not applicable (NA).

### Procedure

#### Overview

This goal of this study is to implement an educational intervention at home for patients who have suffered a stroke, in order to optimize or improve their performance of ADL after discharge from the hospital to their homes. This intervention will be divided into two stages. In stage 1, assessments will be carried out for the experimental group and the control group, but educational advice will only be provided to the former. Stage 2 comprises a pilot program in which a reminder app will be installed on the mobile phones of some of the participants of the experimental group in order to increase treatment adherence.

#### Stage 1

Stage 1 will begin with the collection of the participants’ demographic data through a questionnaire and by conducting various tests to measure primary and secondary outcome variables. Subsequently, the ergonomics of the home and the implementation of ADL from both the experimental group and the control group will be assessed using the HTAS tool, which was developed by the authors. For the development of the tool, a literature review was performed using the PubMed electronic database and by reviewing different practice guides about stroke. Subsequently, the HTAS tool was evaluated by a panel of experts composed of occupational therapists, physiotherapists, nurses, caregivers, and patients.

Following the assessment of each participant’s home and his or her performance of ADL, the therapist will provide the participants of the experimental group with a list of pieces of advice related to the HTAS tool items that were evaluated negatively. The advice will be aimed at changing the environment in which the participants execute the ADL. This may include facilitation in the execution of the ADL, promoting the active use of the affected side of the body in such execution, or to show them the most appropriate way of performing certain tasks according to their situation after the stroke.

The evaluation of the variables and the execution of the advised tasks will be carried out at participants’ homes 2 and 4 weeks following the initial assessment. Researchers will analyze and compare the data obtained from the outcome variables of the experimental group and the control group to check whether the educational intervention was effective in patients who have suffered stroke and who have been discharged to their homes. If the hypothesis is confirmed, the educational intervention would be implemented in the control group.

#### Stage 2

For the pilot study in stage 2, one group will receive the app reminders on their mobile phones—mobile phone group—and another group will not—no mobile phone group. Placement in the first group depends on whether the participant has a mobile phone and if its characteristics are adapted to the requirements of the study. The app will provide the advice previously given by the therapist in the participants’ homes. The timing of reminders will differ for each participant depending on the amount of advice given. However, in the 4 weeks of the app being used, each piece of advice will be given three times. The mobile phone will beep once for each piece of advice and the participant must check and mark the option indicating whether he has or has not complied with the advice. After this period, the outcome variables will be analyzed in both groups to check whether there are differences between the two groups.

After 8 weeks, and after having removed the app from mobile phones of the mobile phone group, we will reanalyze the outcome variables. Will do this by testing both groups to see whether the mobile phone group participants have continued to perform the advised tasks provided by the therapist, and if differences still exist between them and the no mobile phone group. If so, a reminder system will be implemented in the no mobile phone group. Figure 2 shows the outline of the entire study protocol, including steps in stage 1 and stage 2.

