### Randomization

In stage 1, the sample will be divided into two groups of 40 participants each—experimental group and control group. The allocation and the randomization will be performed by a blinded researcher. The assignment of subjects to each group will be made through a system of sealed envelopes. Subsequently, for the pilot study in stage 2, we will create a group that will receive the app reminders on their mobile phones—the mobile phone group—and another group that will not receive the app reminder—the no mobile phone group. Group allocation will depend on whether the participant has a mobile phone and if its characteristics are adapted to the requirements of the study.

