### Statistical Analyses

Descriptive analyses will include mean, standard deviation, and 95% confidence intervals of the values for each variable. The normality of the variables will be performed using the Kolmogov-Smirnov (KS) test. Preintervention values prior to each condition will be compared. A 2x2 mixed-model analysis of variance (ANOVA) with supplementation (mobile phone group or no mobile phone group) as the between-subjects variable, and time (pre- and postintervention) as the within-subjects variable will be used. Intergroup effect sizes will be calculated (Cohen’s d). An effect size <0.2 reflects a negligible difference, between ≥0.5 and ≤0.8 a moderate difference, and ≥0.8 a large difference. A *P* value <.05 will be considered statistically significant. Data will be analyzed using SPSS version 19.0.

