### Sample Size Calculation

A power analysis was conducted using the program G*Power 3.1. A priori, a sample of approximately 40 participants per group for the stage 1 intervention is needed to detect a significant difference (17.3 in the FIM [39]) between the experimental group and the control group (effect size d=0.59, alpha=.05, beta=.08). The randomization will be performed by a blinded researcher.

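### Stage 1 allocates exactly the 40 per group it says it needs, leaving no margin for withdrawal; on the printed inputs that number gives about 74% two-sided power, not 92%, and the one named model is a two-time-point ANOVA for other groups

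*Protocol article*

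**What the plan says.** - **Number needed.** Sample Size Calculation states that "a sample of approximately 40 participants per group for the stage 1 intervention is needed". The inputs are a 17.3-point FIM difference, d=0.59, alpha=.05 and beta=.08. It does not say whether the test is one- or two-sided.
- **Number allocated.** Participants gives a total of 80, and Randomization says that "the sample will be divided into two groups of 40 participants each".
- **Withdrawal.** Ethical Considerations says that the consent form explains to participants "their freedom to leave the study at any time they choose".
- **Stage 1 follow-up.** Procedure, Stage 1, with times counted from baseline: "The evaluation of the variables and the execution of the advised tasks will be carried out at participants’ homes 2 and 4 weeks following". The randomised arms are then to be compared; no test is named there.
- **Stage 2 follow-up.** "After 8 weeks, and after having removed the app from mobile phones of the mobile phone group, we will reanalyze the outcome variables". The place of that assessment is not given.
- **Model.** Statistical Analyses names a 2x2 mixed ANOVA "with supplementation (mobile phone group or no mobile phone group) as the between-subjects variable", with "time (pre- and postintervention) as the within-subjects variable will be used".

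**The concern.** The number needed and the number allocated are the same, so any appreciable loss leaves stage 1 below its own stated basis. That matters more if the number was too small for the printed inputs from the start.

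The planned visits and the named model also do not match. Stage 1 yields baseline, week 2 and week 4, while the model has two time levels and a between-subjects factor taken from stage 2. If it were carried over to the randomised arms in the usual way, one follow-up would go unused, and anyone lacking the chosen post value would drop out of the comparison.

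Finally, the stage 1 visits are set at home, in people with Barthel scores of 0 to 49 who were discharged within the previous 3 months. Someone back in hospital or living elsewhere at a visit may be missed, and that could be related to dependence, which the main outcome measures. At stake are the power of the randomised comparison and, less certainly, its freedom from bias.

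**Working it through.** **Inputs.** From the article: d=0.59, alpha=.05, beta=.08 (power 1 − 0.08 = 0.92), 40 per group. Assumed: a two-sided test with one-sided shown beside it, and losses of 10% and 20%, because the article gives no loss rate.

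**Step 1: the plan's own figure.** For two means, n per group = 2(z₁₋α/₂ + z_power)² / d². Two-sided at 92%: 2(1.960 + 1.405)² / 0.59² = 65.06, so 66. The figures in brackets use the noncentral t.

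| Test | 92% power | 80% power |
|---|---|---|
| Two-sided | 66 (67) | 46 (47) |
| One-sided | 54 (55) | 36 (37) |

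None of these is 40.

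**Step 2: power with 40 per group and after loss.** Power ≈ Φ(d√(n/2) − z). For n=40, two-sided: d√(n/2) = 0.59 × √20 = 2.639, and Φ(2.639 − 1.960) = 0.751. The noncentral t gives 0.741. All noncentral t values:

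| Analysed per group | Assumed loss | Two-sided | One-sided |
|---|---|---|---|
| 40 | 0% | 0.741 | 0.834 |
| 36 | 10% | 0.695 | 0.798 |
| 32 | 20% | 0.642 | 0.755 |

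Losses of 10% and 20% cost about 5 and 10 percentage points two-sided.

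**Step 3: is a reserve hidden in the 40?** One-sided at 80% power with 10% loss gives 36/0.9 = 40. That would contain a reserve, but 80% power contradicts the printed beta and neither the one-sided test nor the 10% is stated. To finish with 40 analysed, 40/0.9 = 44.4, so 45, would have to be allocated at 10% loss, and 40/0.8 = 50 at 20%.

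**Step 4: does the pre/post design rescue the figure?** Suppose d is scaled to the raw SD and the test is on change from baseline. The variance is then multiplied by 2(1 − ρ), where ρ is the pre/post correlation, which the article does not give. At two-sided alpha .05 and 92% power:

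- ρ=0.5: factor 1, so 66 per group
- ρ=0.7: factor 0.6, so 65.06 × 0.6 = 39.04, rounded up to 40

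Under ρ=0.7 the stated number is met exactly, again with nothing to spare: power is 0.920 with 40, 0.890 with 36 and 0.851 with 32. With baseline as a covariate the factor is 1 − ρ²: 49 per group at ρ=0.5, and 34 at ρ=0.7. Only that last case leaves room for loss, of 40 − 34 = 6 per group.

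**Step 5: visits against model.**

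| | Stage 1 procedure | Named model |
|---|---|---|
| Groups | Experimental and control | Phone and no phone |
| Occasions | Baseline, week 2, week 4 | Pre and post |

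A conventional 2x2 repeated-measures ANOVA needs both values from each participant. With week 4 as post, someone seen at baseline and week 2 only would contribute nothing.

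**The case against.** The strongest reply is that this is a condensed article. Rules for missed visits, withdrawal and missing data commonly sit in the full protocol or analysis plan, neither of which is shown. That stands, and the point does not rest on their absence. It rests on the printed calculation, the fixed allocation and the named model.

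The article says approximately 40, so losing one person does not break the plan. That also stands. Step 4 further shows that a strong pre/post correlation could justify 40, or even leave a small reserve. No correlation is stated, however, and the section describes a d for the difference between two groups, so the plain two-group reading is the natural one.

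The ANOVA is written for the phone groups. Its use for stage 1 is therefore conditional: it is the only inferential model named, but the article does not say it will be applied there.

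Three stronger readings are tempting, and the article supports none of them:

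- **That everyone readmitted, relocated or withdrawn is lost.** The text gives a place for the stage 1 visits. It states no exclusion and rules out no other route. Home assessment also follows from the aim of improving daily activities in the home.
- **That the worst outcomes are lost selectively.** No rate or pattern of loss is given. Any bias figure would need an assumed imbalance between arms and an assumed gap in Barthel score. With equal loss and the same gap in both arms, the bias would be zero.
- **That people who stop following the advice yield no outcome.** Carrying out the advised tasks is itself assessed at the visits; it is not a condition for being assessed. The control group receives no advice during stage 1.

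**Conclusion.** The point holds in this limited form. The number needed equals the number allocated, withdrawal is foreseen, and no margin is stated. On the printed d, with a plain two-group comparison at two-sided alpha .05, power is about 74% with no loss instead of 92%, and about 69% or 64% if 10% or 20% are lost. One-sided power is about 83%, 80% or 75%, still short of 92%. These figures rest on assumed loss rates and on no gain from the baseline value. A correlation of 0.7 with a change-score test would restore the printed figure at full retention, but the article does not state it.

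The two-time-point model, if carried over to the randomised arms, would leave one follow-up unused and restrict the comparison to participants with both values. Loss of people not at home, and its link to dependence, is a risk to plan for and not something the article establishes. The change should be made, but the trial does not fail without it.

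**What to change.** - **Sample Size Calculation.** Call 40 per group the number randomised. State whether the test is one- or two-sided and, if the calculation relied on it, the pre/post correlation. Restate the power delivered over a range of completers, for example 40, 36 and 32 per group.
- **Statistical Analyses.** Name the analysis of the stage 1 randomised arms: a likelihood-based repeated-measures model using baseline, week 2 and week 4, with every participant in the allocated arm. It uses partial data and both follow-ups. It does not by itself remove bias if loss depends on unseen outcomes, which is why the next item matters.
- **Procedure, Stage 1.** Where a home visit is not possible, obtain the Barthel Index by telephone or from a carer. The physical performance tests cannot be replaced this way and would stay missing.

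The cost is protocol wording and a telephone or carer form of the Barthel Index. The downsides are some mixing of assessment mode and, on the plain two-group reading, a less favourable stated power. No participants are added.

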**Figure 2 figure2:**
[figure not shown]
Flowchart of the study protocol. MPG: mobile phone group, NMPG: no mobile phone group.

### Statistical Analyses

Descriptive analyses will include mean, standard deviation, and 95% confidence intervals of the values for each variable. The normality of the variables will be performed using the Kolmogov-Smirnov (KS) test. Preintervention values prior to each condition will be compared. A 2x2 mixed-model analysis of variance (ANOVA) with supplementation (mobile phone group or no mobile phone group) as the between-subjects variable, and time (pre- and postintervention) as the within-subjects variable will be used. Intergroup effect sizes will be calculated (Cohen’s d). An effect size <0.2 reflects a negligible difference, between ≥0.5 and ≤0.8 a moderate difference, and ≥0.8 a large difference. A *P* value <.05 will be considered statistically significant. Data will be analyzed using SPSS version 19.0.

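### The only model with named factors tests the non-randomised phone contrast; the randomised experimental-versus-control comparison has no stated test

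*Protocol article*

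**What the plan says.** **The model.** The Statistical Analyses section of the protocol article specifies a 2x2 mixed-model ANOVA "with supplementation (mobile phone group or no mobile phone group) as the between-subjects variable". Its other factor is time, with two levels, before and after the intervention. The rest of the section gives descriptive statistics, a normality check, a comparison of baseline values with no named test, Cohen's d, a .05 threshold and the software. The abstract repeats the 2x2 ANOVA without naming its factors.

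**The randomised comparison.** The Randomization section says: "In stage 1, the sample will be divided into two groups of 40 participants each—experimental group and control group". Under Procedure, Stage 1, "Researchers will analyze and compare the data obtained from the outcome variables of the experimental group and the control group", with follow-up assessments that "will be carried out at participants’ homes 2 and 4 weeks following the initial assessment". If the hypothesis is confirmed, the controls are to receive the intervention as well. The Sample Size Calculation section sizes the trial on the experimental-versus-control difference.

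**The phone groups.** Stage 2 is described as a pilot. The Randomization section says of it: "Group allocation will depend on whether the participant has a mobile phone and if its characteristics are adapted to the requirements of the study". According to the Procedure overview, the app "will be installed on the mobile phones of some of the participants of the experimental group".

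**The concern.** A confirmatory analysis should estimate the contrast that was randomised. Here the between-subjects factor is written out with its two levels, and those levels are the pilot groups. Read literally, the model compares people who own a suitable phone with people who do not. In stroke survivors, phone ownership may well go with age, cognition, dependency and family support, so a difference between these groups cannot be credited to the app by design. It says nothing about the educational advice either.

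At stake is the trial's main conclusion. With no test attached to the stage 1 comparison, the model and the time point can still be chosen after the data are seen. So, in effect, can the leading outcome, because two instruments have a claim to that place. The decision to extend the intervention to the controls depends on the result.

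**Working it through.** The point has no figure of its own to reproduce. The sample size matters here only because it shows which contrast was planned; whether that calculation is right is a separate question. The check sets the sections side by side.

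**Step 1: which contrast each part of the protocol article concerns**

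| Section | Contrast |
|---|---|
| Introduction, aim and hypothesis | Effect of the educational intervention; the app is a secondary aim |
| Randomization, stage 1 | Experimental vs control, 40 + 40 = 80, by sealed envelopes |
| Sample Size Calculation | Experimental vs control, stage 1, 17.3 on the FIM, d = 0.59 |
| Procedure, Stage 1 | Experimental vs control, with a decision about controls attached; no test named |
| Procedure, Stage 2 | Phone vs no phone; a pilot, not randomised |
| Statistical Analyses | Phone vs no phone; the only model with named factors |

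The first four rows agree with one another. The last row agrees only with the pilot.

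**Step 2: what the stated model estimates.** A 2x2 mixed ANOVA has a group effect, a time effect and a group-by-time interaction. With phone versus no phone as the group, the interaction is the difference in pre-to-post change between phone and no-phone participants. No term contains experimental versus control. The randomised effect is therefore not a parameter of this model, whatever the sample size.

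**Step 3: would replacing the factor be enough?** No. Stage 1 has a baseline and two follow-ups, 1 + 2 = 3 assessments. The model has 2 time levels, and nothing says whether the post-intervention level is week 2 or week 4.

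**Step 4: is the outcome settled?** Not fully. Table 1 marks the Barthel Index as the main variable and the FIM as secondary, yet the sample size rests on the FIM. Two follow-up visits and two candidate outcomes give 2 x 2 = 4 possible leading comparisons, before any choice of test.

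**The case against.** The strongest reply is that the ANOVA sentence describes the stage 2 analysis. Procedure, Stage 2 does plan a phone versus no-phone comparison, and for that purpose the factor is correct. On this reading the stage 1 test is simply not mentioned, and a condensed article may leave it to a fuller document.

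Part of this stands. The phone factor suits the stage 2 question and need not be deleted. The reply does not remove the problem, because nothing limits the model to stage 2: both the abstract and the Statistical Analyses section present the 2x2 ANOVA as the trial's model. An article that fixes design, factor and levels has gone past the point where the matter is merely left open.

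Three stronger readings are tempting but not supported:

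- *The main hypothesis cannot be tested.* Procedure, Stage 1 plans the experimental-versus-control comparison, and the planned Cohen's d values between groups are not restricted to the phone groups. What is absent is a stated test, not the intention to compare.
- *Only one P value arises from the plan.* The section also includes normality tests, a baseline comparison and a general significance threshold, and the stage 1 comparison would presumably be tested too.
- *The stated model has a calculable loss of power because it uses only half the sample.* App recipients come from the experimental arm, but the source of the no-phone group is only inferred, and no split is given. The planning d = 0.59 was set for education versus no education; nothing supports applying it to the app.

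**Conclusion.** The point holds in this form: the only inferential model with stated factors is built on the non-randomised pilot contrast, while the randomised comparison that carries the aim, the sample size and the decision about controls is planned without a stated test. Run as written, the model would not estimate the randomised effect.

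This is a mismatch between sections and not merely a missing detail. Its size is categorical: the model addresses a different question, so no number of participants would make it answer the primary one. The conclusion rests only on the wording of the sections compared. It does not depend on where the no-phone participants come from: even if controls entered that group, the factor would still not be the randomised arm. An analysis plan not shown here may already name the stage 1 test; if so, the article should be brought into line with it.

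**What to change.** In the Statistical Analyses section:

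1. State that the primary analysis has randomised arm (experimental vs control) as the between-subjects factor, with all 80 participants analysed as randomised and the Barthel Index, the main variable in Table 1, as outcome.
2. Name one primary stage 1 time point, or use a 2x3 structure covering baseline, 2 weeks and 4 weeks. Week 4, the last stage 1 visit, is a reasonable proposal; the article does not itself make that choice.
3. Reconcile the Barthel outcome with the FIM-based sample size, either by justifying the size for the Barthel Index or by explaining why the FIM was used.
4. Keep the phone versus no-phone ANOVA as a separate stage 2 analysis, labelled exploratory and non-randomised.

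Items 1 and 4 are wording changes. Items 2 and 3 need decisions by the sponsor, which should be recorded before outcome data are compared by arm. No new data collection or extra participants are needed to name the right factor; item 3 may require the sample-size justification to be redone.
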